### Study Population

#### Patients

We will include antipsychotic-naïve people with schizophrenia spectrum first-episode psychosis. Patients will be recruited from psychiatric hospitals and outpatient psychiatric centers in the Capital Region and in Region Zealand of Denmark. Doctor or nursing staff will inform potentially relevant patients about the project, and if he/she accepts, contact the AMEND project medical doctor. Present State Examination (PSE), will be performed by the project medical doctor, to confirm a psychosis diagnosis. Included ICD-10 diagnosis are shown in Table 1. In conjunction, a global evaluation as per general clinical practice will be performed to assess whether antipsychotic treatment is indicated. Patients will be evaluated in cooperation with a senior consultant psychiatrist. Furthermore, a brief somatic and neurological examination, as well as screening for pregnancy and substance abuse, will be performed.

**TABLE 1 T1:** In- and exclusion criteria in AMEND.

Patients
**Inclusion criteria**
+ Antipsychotic-naïve, first-episode psychosis
+ Fulfilling diagnostic criteria of schizophrenia, persistent delusional disorder, acute and transient psychotic disorders, schizoaffective disorder, other non-organic psychotic disorders and unspecified non-organic disorders (ICD-10: F20.x; F22.x; F23.x; F24.x; F25.x; F28; and F29)
+ Age: 18–45 years
+ Legally competent
**Exclusion criteria**
- Current substance dependence ICD-10 (F1x.2) or substance abuse in any period up to 3 months prior to referral (exception: tobacco/nicotine, F17.2)
- Treatment with antidepressants within 30 days
- Head injury with more than 5 minutes of unconsciousness
- Any coercive measure
- Metal implanted by operation
- Pacemaker
- Pregnancy (assessed by urine HCG)
- Female patients: Unwillingness to use safe contraception (Intra Uterine Device/System or hormonal contraceptives) during the study period.
- Severe physical illness
- Allergies to any of the inactive ingredients and film coat components

**Healthy controls (*N* = 20) matched on age and gender**
**Inclusion criteria**
+ No first-degree relative with known major psychiatric disorder (ICD-10: F1x; F2x; and F3x)
+ Age: 18-45 years
+ Legally competent
**Exclusion criteria**
- Lifetime substance abuse/dependence ICD-10 (F1x.1/F1x.2) (exception: tobacco/nicotine, F17.1/F17.2)
- Head injury with more than 5 minutes of unconsciousness
- Lifetime treatment with antidepressants
- Metal implanted by operation
- Pacemaker
- Pregnancy (assessed by urine HCG)
- Females: Unwillingness to use safe contraception (Intra Uterine Device/System or hormonal contraceptives) during the study period.
- Severe physical illness

Patients will receive no economical compensation for participation as remuneration is not allowed according to Danish regulations. The medication will be provided free of charge and transportations costs will be covered.

#### Healthy Controls

Twenty healthy controls (HC) matched 1:2 on age, sex, ethnicity and parental socioeconomic status will be recruited through online advertisement per website.^1^ Healthy controls will receive a taxable disadvantage allowance of DKK 1,000 for completion of the baseline visit and DKK 2,000 for the end of trial visit.

In- and exclusion criteria are shown in Table 1.

#### Trial Visits and Examinations

At baseline in the antipsychotic-naïve state as well as after 12 weeks of treatment, patients will undergo detailed examination program including: (1) clinical ratings and assessments, (2) neurocognitive testing, and (3) Magnetic Resonance Imaging (MRI) scans. Between week 0 and week 12 regular clinical examinations will be undertaken, see examination program Table 2.

**TABLE 2 T2:** AMEND examination program.

[figure not shown]

*

Patients 

Patients and healthy controls*

*
**Clinical examinations:**
*

*Diagnosis/symptoms: Schedules for Clinical Assessment in Neuropsychiatry (SCAN), Positive And Negative Syndrome Scale (PANSS), Brief Negative Symptom Scale (BNSS), Calgary Depression Scale for Schizophrenia (CDSS).*

***Level of functioning:** Clinical Global Impression (CGI), Global Assessment of Functioning (GAF), Personal and Social Performance Scale (PSP).*

*Side effects/quality of life: Udvalg for Kliniske Undersøgelser (UKU) (measurement of side effects), Changes in Sexual Functioning Questionnaire (CSFQ), Quality of Life Scale (QLS).*

***Other:** Edinburgh Handedness Inventory (EHI). Total duration, clinical assessments: 2.5–3 h.*

*Physiology:*

*Fasting blood samples include: Fasting plasma glucose, HbA1c, triglyceride, total cholesterol, LDL cholesterol, VLDL cholesterol, HDL cholesterol, prolactin, *se-amisupride, *se-memantine (*follow-up only).*

*Body Mass Index (BMI).*

*Total duration, clinical assessments: 15 mins.*

*
**Cognition:**
*

*-Brief Assessment of Cognition in Schizophrenia (BACS): memory, working memory, processing speed, executive functions and verbal fluency (35–40 min).*

*-Cambridge Neuropsychological Test Automated Battery (CANTAB) (selected tests): Rapid Visual Information Processing (RVP) (attention), Spatial Working Memory (SWM) (working memory), Paired-Associates Learning (PAL) (visuo-spatial associative learning, i.e. ‘what, when and where’) (25-27 min).*

*-Danish Adult Reading Test (DART): premorbid IQ measure (5–6 min).*

*Total duration, cognition: 65-75 min.*

*
**Magnetic resonance spectroscopy (MRS):**
*

*Magnetic Resonance Spectroscopy measurements will performed Danish Research Centre for Magnetic Resonance (DRCMR) on a whole-body 7 T MR scanner (Achieva; Philips, Cleveland, OH, United States) using a 2-channel volume transmit head coil and 32-channel receiver array (Nova Medical, Inc, Burlington, MA, United States).*

*Voxel placement is planned in five a priori selected regions if interest (ROIs): thalamus, anterior cingulate cortex (ACC), hippocampus, dorsolateral prefrontal cortex (DLPFC), and basal ganglia (32–34).*

*MRS analyses will be performed in LCModel (Provencher, 1993) as also used in Bojesen et al. (9), Reid et al. (33), and Wang et al. (34).*

*Measurements of brain metabolites include: glutamate, glutamine, γ-aminobutyric acid (GABA), N-acetylaspartate, N-acetylaspartyl glutamate, and glutathione (33, 34).*

*Total duration, MRS: 60 min.*

#### Clinical Ratings

Symptom severity will be assessed by the Positive and Negative Syndrome Scale (PANSS) (46). Moreover, the primary clinical endpoint, PANSS negative symptoms, will be supplemented by the Brief Negative Symptom Scale (BNSS) (47). As descriptive and explorative endpoints, quality of life will be evaluated using the Quality of Life Scale (QLS) (48). The UKU side effect rating scale (49) and Changes in Sexual Functioning Questionnaire (CSFQ) (50) will be used to asses potential side-effects. Handedness will be assessed with Edinburgh Handedness Inventory (EHI) (51). Level of functioning will be evaluated with the Personal and Social Performance Scale (PSP) (52), and Global Assessment of Functioning (GAF) (53). The Clinical Global Impression (CGI) (54) will be used to assess the patients’ overall illness severity.

Based on previous studies in similar patient populations we expect the mean PANSS negative symptom score to reside around 20, eg. (9, 55) and in order to enhance generalizability to this patient population, we did not set a minimal level of symptoms.

In order to retain comparability to other studies, e.g.,(42–44) we opted for PANSS. To address the controversy regarding of PANSS negative symptoms, we employ BNSS as secondary endpoint. We recently validated BNSS for use in Danish settings (56, 57).

#### Cognitive Testing

Specific cognitive functions will be examined using selected tasks from The Cambridge Neuropsychological Test Automated Battery (CANTAB) (58–60) and The Brief Assessment of Cognition in Schizophrenia (BACS) (61, 62). Both batteries are well validated and have previously been applied in patients with schizophrenia, e.g., (26, 63–68).

From CANTAB we will include Spatial Working Memory (SWM) to assess visual working memory, Paired Associated Learning (PAL) to assess visual learning, and Rapid Visual Information Processing (RVP) to assess sustained attention. BACS will be used to assess verbal learning, verbal working memory, processing speed, planning and verbal fluency. Finally, premorbid intelligence (IQ) will be estimated using the Danish version of the National Adult Reading Test (DART) (69) (adapted from the National Adult Reading Test, NART) (70).

### Magnetic Resonance Imaging and Magnetic Resonance Spectroscopy

Magnetic resonance imaging scans will be performed at the Danish Research Centre for Magnetic Resonance (DRCMR), Copenhagen University Hospital Amager and Hvidovre, on a whole-body 7 Tesla (7T) MR scanner (Achieva; Philips, Cleveland, OH, United States) using a 2-channel volume transmit head-coil and 32-channel receiver array (Nova Medical, Inc., Burlington, MA, United States). MRS will be used to assess glutamate levels pre – and post treatment in five preselected regions of interest: anterior cingulate cortex (ACC), dorsolateral prefrontal cortex (DLPFC), thalamus, hippocampus, and the basal ganglia. In addition, T1- and T2 weighted structural images and diffusion sensitive sequences will be performed to explore cortical and subcortical brain structures, and the integrity of white matter tracts. Quantitative Susceptibility Mapping (QSM) will be used to estimate regional iron accumulation, and measurement of the neuromelanin (NM) concentration will be performed in substantia nigra (SN) as a proxy for structural and functional integrity of dopaminergic cells (36).

Our group has established a robust 7T protocol for glutamate MRS at our 7T MR system and validated the protocol in a cohort on healthy individuals in a study on normal cognitive aging (71, 72).

We will apply this optimized MR protocol in the AMEND study on a Philips 7T whole body MR scanner (Philips) using a dual transmit coil and a 32-channel receive head coil (NovaMedical). We will use a sLASER sequence (73) with a TR/TE = 3700/32 ms, bandwidth = 4 kHz, data points = 2048) with prospective frequency and motion correction.

For structural MRI, we will use a tailored acquisition protocol which we have successfully applied to map the SN and LC at high resolution and signal-to-noise ratio in a cohort of patients with Parkinson’s disease and age-matched controls. The neuroimaging results regarding the Locus coeruleus have been recently published (74). In addition to locus coeruleus mapping, this structural 7T MR protocol also provides exquisite high-resolution maps of the substantia nigra (unpublished data). In short, the structural MRI protocol includes a T1-weighted(T1w), high-resolution (1-mm isotropic) and a magnetization transfer weighted, three-dimensional, high-resolution (voxel size, 0.4 × 0.4 × 1.0 mm) ultra-fast gradient echo sequence (echo time/repetition time = 4.1/8.1 ms, flip angle = 7 degrees, two averages). Magnetization transfer saturation will be achieved by applying 16 block-shaped pre-pulses at a frequency offset of 2 kHz (flip angle = 278 degrees, duration = 10 ms). We will also acquire T1-weighted images with identical acquisition parameters for co-registration purposes, but with a zero-degree flip angle for the off-resonance pre-pulse.

### Intervention

#### Amisulpride

Tablet *amisulpride* is a second-generation antipsychotic and a first-line, generic drug against psychosis and schizophrenia in Denmark (75). Amisulpride primarily binds to dopamine D2 and D3 receptors, but also has affinity for serotonin 5-HT7 receptors (76). In AMEND, amisulpride is used as “tool compound” because it is the most selective licensed antidopaminergic compound to treat psychosis. All patients will be treated with tablet amisulpride with initial dose 50–100 mg/day. Doses will be slowly augmented according to effect and side-effects to a maximum of 800 mg/day.

#### Memantine vs. Placebo

Tablet *memantine* is approved for treatment of Alzheimer’s Disease (AD) showing benefits on the main domains of AD i.e.,. cognition, function, behavior, and clinical global change (77). Memantine acts through uncompetitive, open-channel NMDAR antagonism, and has minimal activity for GABAergic, dopaminergic, adrenergic, histaminergic, and glycinergic receptors.

Patients will be blindly randomized to treatment with either memantine or placebo. Treatment will be initiated at 10 mg/day for 1 week, and from the second week the dose will be increased to 20 mg/day until end of trial. Tablets will be identical, provided in 10 mg or 20 mg tablets, and labeled by the Hospital Pharmacy (Region Hovedstadens Apotek) according to GCP-guidelines; marked with trial reference number, trial subject reference, dosage, administration route, storage and expiration date.

### Randomization

The Hospital Pharmacy will be responsible for randomization, which will be conducted 1:1. Randomization will be stratified by PANSS negative sub-score, categorizing patients in either [Low PANSS negative baseline <20] or [High PANSS negative baseline ≥20].

The randomization will use permuted blocs in sizes of 4,6 and 8 to ensure an even distribution among the two groups. The number of patients in each group will not be restricted. In need of unblinding of a patient’s treatment, the pharmacy can be contacted at any time.

Intolerable side-effects or clinical worsening (defined as a 20% increase in PANSS positive subscale score compared to baseline PANSS positive score) will result in discontinuation of study treatment and study exclusion. Patients will be consulted with the senior consultant psychiatrist associated to the research project and further treatment will be initiated according to general treatment guidelines respecting the patients’ autonomy and requests.

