#### Secondary Endpoints

Secondary endpoints include changes in cognition (in particular working memory, learning and processing speed, and sustained attention), PANSS positive and total-scores, other clinical measures, level of functioning, adverse effects, and glutamate levels in the five *a priori* selected regions of interest mentioned above. Additionally, dopamine function in substantia nigra will be explored using NM-MRI techniques (37).

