### Planned Statistical Analyses

Homogeneity of variance between the two groups will be assessed using Levene’s test. Parametric data will be evaluated using parametric testing. Non-normally distributed data or data that exhibit unequal variances will be tested using non-parametric tests as appropriate. Fisher’s or χ2 exact tests will be used for group comparisons between categorical data. The Benjamini-Hochberg procedure will be used to control the type I error rate.

Data analyses on the primary outcome and most of the secondary outcomes will be performed before un-blinding and according to the per-protocol principle. Analyses of adverse events will be performed according to the intention-to-treat principle. Demographic variables and clinical characteristics will be reported in frequency for categorical data, and in mean values (with standard deviations and range) for normally distributed, continuous variables. Group comparisons for demographic data will be performed using independent *t*-tests for continuous variables and Chi-square tests for nominal and ordinal variables. Primary and secondary outcomes will be tested using repeated measures (rm)ANOVA.

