### Power Calculation

The power calculation is based on the primary outcome. We used the most representative clinical study we could identify and attempted to modify to the current setting. An 8-week RCT using risperidone plus memantine in stable schizophrenia patients (*N* = 40) reported a reduction in PANSS negative of −2.8 (SD 1.6) with memantine compared to −0.8 (SD 0.9) with placebo (79). Assuming a similar response, we expect add-on memantine to induce −2 ± 2 point more reduction in PANSS negative compared to amisulpride monotherapy. An *a priori* Student *t*-test (two-sided) with significance level α of 0.05 and a desired power (1-α) of 80%, shows that 16 completed patients in each arm is needed.

To increase power of secondary analyses, enrollment will continue until 18 participants in each arm have completed examinations. Moreover, AMEND will be extended to 12 weeks based on the median trial duration in the meta-analysis of add-on memantine [12 weeks (mean 11.5 weeks)] (42). Based on our center’s 20 years of experience with recruitment and treatment of antipsychotic-naïve patients, we expect an inclusion rate of 2 patients per month and an attrition rate of 25%. Thus, recruitment of 46 patients will take approximately 2 years.

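### PANSS positive is a secondary endpoint, yet a 20% rise in it excludes the patient; if it is analysed per protocol, its comparison understates any excess of psychotic worsening under memantine

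*Protocol article*

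**What the plan says.** Four statements in the protocol article bear on this point.

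- **Secondary Endpoints.** The list includes "PANSS positive and total-scores, other clinical measures, level of functioning, adverse effects".
- **Randomization.** One trigger for stopping the trial medication and leaving the study is "clinical worsening (defined as a 20% increase in PANSS positive subscale score compared to baseline PANSS positive score". Intolerable side effects are named there as a separate reason.
- **Planned Statistical Analyses.** "Data analyses on the primary outcome and most of the secondary outcomes will be performed before un-blinding and according to the per-protocol principle". The test is given as well: "Primary and secondary outcomes will be tested using repeated measures (rm)ANOVA". For safety, "Analyses of adverse events will be performed according to the intention-to-treat principle".
- **Power Calculation.** "enrollment will continue until 18 participants in each arm have completed examinations". Expected attrition is 25%, not divided by reason or arm, and recruitment is put at 46 patients.

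The endpoint sections do not list removal for clinical worsening as an outcome.

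**The concern.** The scale that measures psychotic worsening also decides who leaves. A patient whose PANSS positive score rises by 20% is excluded, a per-protocol analysis omits that patient, and recruitment continues until a completer fills the place. The upper tail of the endpoint is cut off by the endpoint's own value. If the arms differ in how often patients cross the line, the comparison of those who remain is pulled towards no difference. The pull works in both directions, so a protective effect of memantine against exacerbation would be understated too.

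This differs from ordinary missing data on the primary endpoint, because here the reason for leaving is the outcome itself. It matters because, according to the Introduction, the proposed effect of memantine has not been studied in initially antipsychotic-naïve patients, and the Discussion only assumes that the benefit seen in chronic patients carries over. A PANSS positive result of no difference would be read as reassurance, although the exclusion rule could have produced it.

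**Working it through.** **What the article supplies.** It gives the 20% rule, the endpoint list, the analysis sets, the completer target and 46 recruits at 1:1, so 46/2 = 23 per arm. It gives no PANSS positive baseline, SD, expected change or removal rate. There is therefore no stated figure to reproduce on this point, and everything below rests on assumed inputs.

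**Assumed inputs.** Baseline PANSS positive has mean 20 and SD 4. The usual change over 12 weeks is −5, with SD 5 unless stated. Scores are rounded. A patient is removed if the final score is at least 1.2 × baseline; at a baseline of 20 the line is 1.2 × 20 = 24, a rise of 4 points. The rule is applied once, to the final score. This is a simplification, since ratings between visits could also trigger removal.

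**Quantities compared.** The true difference is the mean change on memantine minus that on placebo in all simulated patients. The analysed difference is the same contrast in patients not removed. Share lost = 1 − analysed/true.

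| Assumed form of worsening (memantine v placebo) | True | Analysed | Share lost |
|---|---|---|---|
| Net rise of about 8 points instead of the usual −5, in 20% v 5% | 1.90 | 0.11 | 1 − 0.11/1.90 = 94% |
| 10 points added to the patient's own change, in 20% v none | 1.94 | 0.54 | 1 − 0.54/1.94 = 72% |
| 8 points added, in 20% v 5% | 1.15 | 0.48 | 1 − 0.48/1.15 = 58% |
| 5 points added, in 40% v 10% | 1.41 | 0.88 | 1 − 0.88/1.41 = 38% |
| Every memantine patient 2 points worse | 1.87 | 1.45 | 1 − 1.45/1.87 = 22% |

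The last row falls to 13% if the SD of change is 4.

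**Why the first row is so large.** Affected patients there end 8 − (−5) = 13 points worse than usual, and (0.20 − 0.05) × 13 = 1.95, close to the simulated 1.90. A rise of 8 lies well above the removal line of 4, so nearly all of the harm falls among patients who are dropped. The result depends on how tightly the rises cluster. Repeating the row with the net rise drawn with SD 3 gives 1.89 against 0.14 (93% lost), and with SD 5 it gives 1.90 against 0.25 (87% lost). Removals in the first row are about 22% v 9%.

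**Check with no harm.** With identical arms the true and analysed differences are both about 0. The rule does not create a difference; it shrinks one that exists.

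**What a count of removals could show.** With 23 per arm and a two-sided Fisher test at 0.05:

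- 4 v 0 removals gives p = 0.11, and 5 v 0 gives p = 0.049.
- Power is 22% for 20% v 5%, 53% for 30% v 5%, and 80% for 40% v 5%.

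**The case against.** A reader might infer that psychotic worsening under memantine cannot appear in the results at all, or that removals are compared nowhere. The documents do not support either reading, for these reasons.

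- **Adverse events.** Adverse effects are a secondary endpoint and adverse events are analysed by intention to treat, so removed patients stay in that set. If clinical worsening is recorded as an adverse event, it will show there. Naming it apart from side effects under Randomization does not rule this out. This stands, but the safeguard depends on a recording choice that the article does not state.
- **The word most.** The article does not name the secondary outcomes that escape the per-protocol rule, and PANSS positive could be one of them. This stands, and the conclusion is conditional for that reason.
- **Smaller rises.** Patients who worsen by less than 20% remain in the data. This stands, and the table shows that a general worsening is mostly preserved.
- **A condensed article.** Tables of discontinuation by reason and arm are commonly left to the full protocol or analysis plan, so their absence here is no defect. This stands too. The point rests on what the article does fix: the exclusion rule, the endpoint, the analysis set and the completer target.
- **Size.** A reader might take the loss of about 95% as the expected size. It belongs to one form of harm, a subgroup with large net rises, and none of its inputs is in the article.

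It can also be said that this is one consequence of analysing per protocol after post-randomisation exclusions, and that an all-randomised analysis would repair much of both problems. That is fair. The PANSS positive case still needs its own sentence, because here the exclusion is defined by the endpoint's own value.

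**Conclusion.** The point holds in a conditional form. If PANSS positive is among the outcomes analysed per protocol, the plan selects a harm-relevant endpoint on its own value, and the bias is towards no difference in psychotic worsening. The total score, which contains the positive items, is affected in the same direction. Under the assumed inputs the loss runs from about 13% of the true arm difference to over 90%, depending mainly on whether the harm is a small general shift or a subgroup with large exacerbations. The direction follows from the stated rules; the size does not, because the article gives no PANSS positive figures. The plan should be changed on this point, but the flaw does not undermine the primary comparison by this route alone.

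**What to change.** Leave the clinical stopping rule untouched and change only the analysis.

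1. Analyse PANSS positive and total in all randomised patients, keeping the rating that triggered removal. One option carries it as the patient's last value, which fits the planned repeated-measures ANOVA. Another gives such patients the worst ranks, which needs a rank-based comparison. Choose one before unblinding.
2. Report the per-protocol result as supporting, and state that it will not be read as evidence of no worsening.
3. Count removals for clinical worsening by arm in all randomised patients, with an exact confidence interval for the risk difference, as a descriptive safety outcome. Say whether such a removal is also recorded as an adverse event.

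The cost is a few lines of wording and one more table. No visit or measurement is added, because the rule can only operate on a PANSS positive rating already taken. The downsides are a last-value or worst-rank assumption and a wide interval: at 23 per arm, power for 20% against 5% is only about 22%, so the count can reveal a large excess but cannot exclude a moderate one.

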### Data Analysis

#### Primary Endpoint

The primary endpoint will be reduction in negative symptoms as measured with the negative symptom score from the Positive and Negative Syndrome Scale (PANSS) (78). Reduction in negative symptoms after 12 weeks of treatment: [PANSS negative baseline–PANSS negative at week 12]. PANSS negative assessments will be supplemented by Brief Negative Symptom Scale (BNSS) scores (57).

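### Stopping study treatment for side effects or worsening also ends study participation, so the week-12 primary outcome is lost through post-randomisation events that treatment may affect

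*Protocol article*

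**What the plan says.** The Randomization section of the protocol article names two triggers: intolerable side effects and clinical worsening, the latter "defined as a 20% increase in PANSS positive subscale score compared to baseline PANSS positive score". Either one "will result in discontinuation of study treatment and study exclusion". The patient sees the senior psychiatrist, and "further treatment will be initiated according to general treatment guidelines respecting the patients’ autonomy and requests". No later study assessment is mentioned for these patients.

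The Primary Endpoint section defines the outcome as "PANSS negative baseline–PANSS negative at week 12", so it cannot be computed without a week-12 rating.

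Planned Statistical Analyses states: "Data analyses on the primary outcome and most of the secondary outcomes will be performed before un-blinding and according to the per-protocol principle". Intention-to-treat is named for one purpose only: "Analyses of adverse events will be performed according to the intention-to-treat principle".

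The Power Calculation section continues enrolment until 18 patients per arm have completed. It adds "we expect an inclusion rate of 2 patients per month and an attrition rate of 25" per cent, and plans to recruit 46.

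**The concern.** Stopping a study drug and leaving a study are different events, and the text makes the second follow automatically from the first. Tolerability and symptomatic worsening occur after randomisation, and add-on memantine could change either. If outcome data end at those events, the patients with a week-12 rating are a selected subset in each arm, and randomisation no longer guarantees that the subsets are comparable.

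Two other choices point the same way. A per-protocol primary analysis would leave these patients out anyway, and enrolling to a completer target replaces them with others who stay. The trial would then describe patients who tolerated treatment and did not worsen. On the same reading, scheduled side-effect ratings after exclusion are lost too, although adverse events are to be analysed by intention-to-treat. An analysis plan written later cannot restore a rating that was never taken.

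**Working it through.** **Inputs from the protocol article.** Difference 2 points, SD 2, two-sided alpha 0.05, power 80%, 16 completers needed per arm, 18 per arm targeted, 25% attrition, 46 recruited (Power Calculation). Allocation 1:1 (Randomization), so 23 per arm.

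**Inputs assumed, because the article gives none.** The split of attrition between arms (memantine *d_m*, placebo *d_p*), and the gap *g* in mean PANSS negative reduction between completers and leavers.

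**1. The plan's own figures.** The normal approximation gives n = 2 × (1.96 + 0.84)² × (2/2)² = 15.7, so 16 per arm, as stated. The exact t-test gives 16.7, so 17. For 36 completers at 25% attrition, 36/0.75 = 48 and 36 × 1.25 = 45; the stated 46 lies between. Expected patients without a week-12 outcome: 46 × 0.25 = 11.5.

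**2. Bias in the completer difference.** In one arm the mean over all patients is (1 − d) × completer mean + d × leaver mean, so the completer mean exceeds it by d × g. With the same g in both arms, bias = g × (d_m − d_p).

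| Attrition memantine / placebo (assumed) | g = 2 | g = 4 |
|---|---|---|
| 25% / 25% | 0 | 0 |
| 30% / 20% | 0.2 | 0.4 |
| 35% / 15% | 0.4 | 0.8 |
| 20% / 30% | −0.2 | −0.4 |

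A more uneven split would give more. For scale, the standard error of the difference with 18 per arm is 2 × √(2/18) = 0.67 points.

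**3. Simulation under no true effect.** 23 randomised per arm, SD 2, attrition 35%/15%, 6,000 runs, t-test on the change among those remaining. Exclusion is driven by a latent course that correlates with the PANSS negative change.

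| Correlation | Mean bias (points) | Two-sided type I error |
|---|---|---|
| 0.3 | 0.17 | about 5% |
| 0.5 | 0.27 | about 7% |
| 0.7 | 0.41 | about 11% |

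At 25%/25% the error stays near 5% at every correlation tried. The simulation randomises a fixed 46 and does not recruit on to 18 completers per arm.

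**4. An extreme case.** Suppose one arm loses its worst quarter on PANSS negative change and the other loses a random quarter. The normal density at the lower quartile is 0.318, so the mean of the rest rises by 0.318/0.75 = 0.424 SD, or 0.424 × 2 = 0.85 points. The gap between completers and leavers in that arm is (0.318/0.75 + 0.318/0.25) × 2 = 3.39 points, so g = 4 in step 2 is a generous upper value. If the trigger correlates with the outcome at only 0.3, 0.5 or 0.7, the 0.85 becomes about 0.25, 0.42 or 0.59.

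**5. Following everyone.** If the 25% who stop gain no memantine benefit (assumption), the expected all-randomised difference is 2 × 0.75 = 1.5 points. With 23 per arm and SD 2, power is about 70% (t-test; 72% by normal approximation), against 83% (85%) for 18 completers per arm at 2 points.

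**The case against.** The worsening trigger is a rise in PANSS positive, while the outcome is PANSS negative, so a patient can be excluded with stable or improving negative symptoms. The trigger is also a measured score, and an analysis using it could address part of the loss under a missing-at-random assumption. The rule applies identically to both blinded arms, and equal selection leaves the difference unbiased. The 25% is overall attrition; the Discussion section also allows withdrawal at any time without explanation, and those patients would not be recovered. The article does not say in words that ratings cease. The examination schedule in Table 2 and the full protocol are not shown, and an end-of-participation visit could exist.

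All of this stands as a limit on size and certainty. It does not remove the point: nothing shown keeps these patients in follow-up, equal selection in both arms cannot be taken for granted when the triggers may respond to treatment, and missing-at-random cannot be tested without the ratings.

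It is also fair that extra ratings alone would not alter a per-protocol result. That bears on how the fix is built, not on whether one is needed.

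A reader might go further and infer that an intention-to-treat analysis becomes impossible. The documents do not support that. Clinical examinations take place between weeks 0 and 12, and about 75% of patients would still have week-12 data. The all-randomised analysis would instead rest on untestable assumptions about the rest.

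**Conclusion.** The point holds as a design weakness that is cheap to correct. As written, the text ties study exit to treatment stop and so loses the primary outcome through events that treatment may affect.

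Its effect cannot be computed from the documents. About 11 to 12 of 46 patients are expected to lack the outcome for any reason; how many leave through this rule is unknown. The bias is 0 under equal attrition and equal selection, about 0.2 to 0.8 points under the assumed 30%/20% to 35%/15% splits with a gap of 2 to 4 points, and negative if placebo loses more. Even at zero bias the estimate describes completers only.

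Two stronger readings are tempting. One is that the missing patients are exactly those with the worst negative-symptom course; the trigger does not measure negative symptoms, so the link is likely but indirect. The other is that the result shifts by 0.85 points. That figure needs a perfect correlation between trigger and outcome, selection in one arm only, and all attrition arising from this rule. The documents support none of these.

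**What to change.** Leave the treatment-stopping rule unchanged. In the Randomization section, delete the words that add exclusion from the study. State instead that patients who stop study treatment remain in follow-up, if they consent, and have the week-12 PANSS, BNSS and side-effect ratings, with MRI optional.

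Amend Planned Statistical Analyses in the same step, so that PANSS negative is also analysed in all randomised patients using these values. Without this second change the added ratings would not affect any stated analysis of the primary outcome.

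The cost is a short amendment and a small number of extra rating visits, at most about a dozen at the planned attrition, with existing staff and scales. Some patients will decline. The all-randomised effect may be smaller than the planning value, as the 1.5-point, roughly 70%-power example shows, and this should be acknowledged when the analysis is added. The article describes the trial as ongoing, and ratings not taken at week 12 cannot be obtained afterwards.
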